#### Behavioral Tasks

Serial Reaction Time Task was programmed using SuperLab 5 (Cedrus, San Pedro, CA, USA) and will be administered in a laboratory setting, with constant artificial light and without auditory interference. The hand to be used for the learning task will be randomized, and the contralateral hand subsequently will perform the adaptation task. The participants will seat on a chair in front of a computer screen, where four aligned blue squares will be presented simultaneously. As soon as one of these squares turns red (visual cue), participants are supposed to press as fast as possible the corresponding one of four aligned buttons on a keyboard with the corresponding index, middle, ring, or little finger (D2, D3, D4, and D5, respectively) of the selected hand. Immediately after correct key selection, the visual cue disappeared and the trial ends. After an interval of 200 ms, a new visual cue appeared and a new trial begins. Twelve consecutive trials correspond to the sequence that participants had to learn explicitly. The sequence needs to follow a specific set of rules: (a) the same visual cue does not appear two times successively; (b) each visual cue appears three times; and (c) visual cues are pseudo-randomized. The sequence to be learned is: 2–4–1–3–2–4–3–1–2–4–1–3. The same sequence will be used in each of the four experimental conditions: (1) Motor sequence learning (MSL), in which participants learn the sequence; (2) Adaptation (AD), in which participants are required to execute the learned sequence with the opposite hand; (3) Delayed recall (DR), in which the participants are required to recall the adapted sequence execution after a 45-min break; (4) Re-adaptation (RA), in which the participants have to return back to execute the sequence with the hand that originally learned the sequence (as shown in Figure 1). In MSL, participants will be required to learn the 12-item sequence presented in a 13-consecutive series, each series repeated four times with an inter-series-interval of 1 min. The same procedure will be repeated after 5 min. In AD, participants performed the same 13-consecutive series of 12-item sequences four times, with an inter-series-interval of 1 min with the opposite hand. In DR, participants repeated the AD task after 45 min and following another stimulation protocol (according to group assignment). Finally, in RA, participants will perform the 12-item sequence with the “original” hand in 13-consecutive series, will repeat four times with an inter-series-interval of 1 min. Errors, i.e., wrong key strokes, were counted (accuracy). The time taken to select the correct key will be recorded (response time, RT) (Figure 2).

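### Accuracy is defined as a raw error count although MSL has twice the trials of every other condition, so the task effect on errors is an exposure artefact

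*Protocol article*

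**What the plan says.** All the relevant task definitions are in the protocol article under Behavioral Tasks.

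- Sequence length: "Twelve consecutive trials correspond to the sequence that participants had to learn explicitly".
- MSL: participants "learn the 12-item sequence presented in a 13-consecutive series, each series repeated four times with an inter-series-interval of 1 min". The next sentence adds a second pass: "The same procedure will be repeated after 5 min".
- AD: "In AD, participants performed the same 13-consecutive series of 12-item sequences four times", with the opposite hand. No second pass is stated.
- DR: "In DR, participants repeated the AD task after 45 min and following another stimulation protocol".
- RA: the sequence is performed with the original hand "in 13-consecutive series, will repeat four times with an inter-series-interval of 1 min". No second pass is stated.
- Outcomes: "Errors, i.e., wrong key strokes, were counted (accuracy). The time taken to select the correct key will be recorded (response time, RT"). No error rate, percentage or other denominator is given.
- End of a trial: "Immediately after correct key selection, the visual cue disappeared and the trial ends".

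The Statistical Analysis section then puts both accuracy and RT into a two-way repeated measures ANOVA. The factors are group (four pairwise contrasts: G1 v G2, G3 v G4, G1 v G3, G2 v G4) and task, and MSL is one of four task levels.

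**The concern.** A count can be compared across conditions only if the opportunity to err is the same in each. Here one level of the within-person factor offers twice the trials of the other three. A participant whose error rate never changes will still make twice as many errors in MSL, and the ANOVA will read that as a task effect.

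The interaction is also at stake. Stimulation switches between sessions, and the Discussion expects the design to separate encoding from retrieval, so the group-by-task term is where that question is tested. On counts, a given change in error rate is twice as large in MSL as elsewhere, and MSL also contributes more variance.

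The definition of RT raises a smaller matter. A trial continues until the correct key is pressed, so the recorded time on a trial with a wrong press contains the wrong press and its correction. The Abstract predicts faster processing and fewer errors under iTBS; if error trials stay in the RT average, the second can produce part of the first.

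**Working it through.** The article gives no trial totals and no power calculation, so there is no stated figure to reproduce.

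**Trials per condition** (inputs from Behavioral Tasks)

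- AD, DR, RA: 12 x 13 x 4 = 624 each.
- MSL: 624 x 2 = 1,248.
- Ratio: 1,248 / 624 = 2.0.

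**Expected errors at a constant error rate** (rates assumed; expected count = rate x trials)

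| Error rate | MSL | Each other task |
|---|---|---|
| 1% | 12.5 | 6.2 |
| 2% | 25.0 | 12.5 |
| 5% | 62.4 | 31.2 |
| 10% | 124.8 | 62.4 |

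Divided by trials, the two columns are equal.

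**Task main effect.** Simulation assumptions: 10 per group (40 split equally), 4% error rate, Poisson errors, between-person log-SD 0.3, residual log-SD 0.15, split-plot ANOVA with two groups and four tasks. With no true task effect, p < 0.05 for task occurs in 100% of runs on counts and about 5% on rates. A variant with binomial errors and a 2% or 5% error rate gives 100% against 5 to 6%.

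**Interaction.** Take 15% effects that follow the stimulation schedule in the Theta Burst Stimulation section: iTBS lowers errors, cTBS raises them, and sham does nothing. The expected between-group differences in counts (absolute values) are:

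- G1 v G2: 0.04 x 0.15 x 1,248 = 7.5 in MSL and 0.04 x 0.15 x 624 = 3.7 in AD, with 3.7 in the opposite direction in DR and RA. On rates all four are 0.6 percentage points, with a change of sign between sessions.
- G2 v G4: 0 in MSL and AD, and 0.04 x 0.30 x 624 = 7.5 in DR and RA. MSL adds noise but no signal.
- G1 v G3: 0.04 x 0.30 x 1,248 = 15.0 in MSL, 7.5 in AD, and 0 in DR and RA.

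Share of simulated trials in which the interaction is declared:

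| Pattern | Counts | Rates |
|---|---|---|
| No stimulation effect | about 7% | about 5% |
| G1 v G2 | 57% | 66% |
| G2 v G4 | 31% | 60% |
| G1 v G3 | 70% | 60% |
| Uniform 30% reduction in all four tasks | 31% | 5% |

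Repeat runs moved these figures by up to about 3 percentage points. The last row is a false interaction on the rate scale, and it needs an effect that is the same in both sessions.

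**RT.** If error trials are kept, mean RT rises by (share of error trials) x (delay per error). With an assumed 5% share and 400 ms delay this is 0.05 x 400 = 20 ms, common to both groups. The spurious group difference is only the change in that amount: for a 30% error reduction, 0.30 x 0.05 x 400 = 6 ms. Over shares of 2 to 10% and delays of 200 to 600 ms, the range runs from 0.30 x 0.02 x 200 = 1.2 ms to 0.30 x 0.10 x 600 = 18 ms.

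**The case against.** The strongest reply is that the article never says outright that unscaled totals from both MSL passes go into the ANOVA. It calls the variable accuracy, the timeline figure is not shown, and a full protocol or SAP may use rates. This lowers certainty about what will be done. It does not remove the point, because the article does define accuracy, the definition is a count, and that variable is the one named in the ANOVA.

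Three stronger readings are tempting, and the document does not support them.

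- A reader might infer that counts bias the interaction towards false positives, citing the 31% against 5% above. That figure needs one group to have the same proportional effect in all four tasks. The schedule switches each group between active and sham stimulation, so uniformity would require complete carry-over from the first session. Under the schedule's own patterns counts reject less often in two of the three contrasts simulated, and with no stimulation effect the inflation is slight.
- A reader might infer that the stimulation comparisons themselves are biased. Within any one task all groups have the same number of trials, so those contrasts stand.
- A reader might infer that the analysed RT is mis-scored, and by 20 ms. The article says only what is recorded. Whether error trials stay in, and how RT is summarised, is left open, as an article commonly does. The 20 ms is total contamination and not a group difference. RT averaged per trial is also untouched by the imbalance of 1,248 to 624.

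**Conclusion.** The point holds for the error outcome. As accuracy is defined, the task main effect on errors cannot be interpreted: MSL will show twice the errors of the other conditions whatever the error rate, and the test will detect this practically every time. That conclusion rests only on the trial counts in the text and on both MSL passes being counted.

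The interaction test is distorted, with a direction that depends on the pattern of the stimulation effect. The size (from a loss of about 29 percentage points for G2 v G4 to a gain of about 10 for G1 v G3) rests on the assumed 4% error rate, 15% effects, 10 per group and the assumed variances, and is illustrative.

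The RT matter is secondary and conditional: about 6 ms (roughly 1 to 18 ms) for a 30% error reduction, and only if trials with a wrong press are kept.

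**What to change.** State that accuracy is scored per trial presented in each condition, either as wrong key strokes divided by trials or as the proportion of trials whose first press is wrong. The second form also copes with trials that collect more than one wrong press. Enter that rate in the planned repeated measures ANOVA. Both MSL runs should stay in: dropping the first would discard early acquisition directly after stimulation, and the division already equalises exposure. No different model is needed for this purpose, since the rate restores the task test to about 5%.

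In the same passage, state that RT is computed on trials whose first press is correct.

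Neither change affects data collection, provided that individual key presses are logged. The cost is a few words in the outcome definitions and the loss of a few percent of trials from the RT average.

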
**Figure 2 F2:**
[figure not shown]
**(A)** Implementation of Serial Reaction Time Task (SRTT); **(B)** Learning sequence; **(C)** Timeline of tasks. See the text.

The total protocol took maximum of 3 h with a 45-min break between the experimental sessions.

### Statistical Analysis

#### Behavioral Task Analysis

Shapiro–Wilk's statistic supported by visual inspection will be used to test the normality of distribution of all variables. Descriptive statistics of collected data will be reported as mean ± SD for continuous variables and as percentage frequencies for categorical variables. To assess data distribution, the variables will be examined by the Kolmogorov-Smirnov (K-S) test. One-way ANOVA will be used to compare differences in baseline values among groups. The effects of two independent variables (groups: specifically, G1 vs. G2; G3 vs. G4; G1 vs. G3; G2 vs. G4; task; MSL, DA, DR, and RA), on both accuracy and RTs of motor skill learning will be evaluated using two-way repeated measures ANOVA.

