## Abstract

Implicit and explicit motor learning processes work interactively in everyday life to promote the creation of highly automatized motor behaviors. The cerebellum is crucial for motor sequence learning and adaptation, as it contributes to the error correction and to sensorimotor integration of on-going actions. A non-invasive cerebellar stimulation has been demonstrated to modulate implicit motor learning and adaptation. The present study aimed to explore the potential role of cerebellar theta burst stimulation (TBS) in modulating explicit motor learning and adaptation, in healthy subjects. Cerebellar TBS will be applied immediately before the learning phase of a computerized task based on a modified Serial Reaction Time Task (SRTT) paradigm. Here, we present a study protocol aimed at evaluating the behavioral effects of continuous (cTBS), intermittent TBS (iTBS), or sham Theta Burst Stimulation (TBS) on four different conditions: learning, adaptation, delayed recall and re-adaptation of SRTT. We are confident to find modulation of SRTT performance induced by cerebellar TBS, in particular, processing acceleration and reduction of error in all the conditions induced by cerebellar iTBS, as already known for implicit processes. On the other hand, we expect that cerebellar cTBS could induce opposite effects. Results from this protocol are supposed to advance the knowledge about the role of non-invasive cerebellar modulation in neurorehabilitation, providing clinicians with useful data for further exploiting this technique in different clinical conditions.

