### Study Design

The participants will be divided into four groups—age, sex, and educational-matched. All the participants will undergo two experimental sessions on a single-day, separated by a break of 45 min, each one including two behavioral tasks based on a modified SRTT paradigm (51–53). Before each session, patients will be subjected to one specific type of cerebellar TBS (Figure 1).

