#### Theta Burst Stimulation

Group 1 (G1) will receive cerebellar iTBS before the session 1 and sham stimulation before the session 2; group 2 (G2) will receive cerebellar sham stimulation before the session 1 and cerebellar iTBS before the session 2; group 3 (G3) will receive cerebellar cTBS before the session 1 and sham stimulation before the session 2; group 4 (G4) will receive cerebellar sham stimulation before the session 1 and cerebellar cTBS before the session 2 (as shown in Figure 1).

Theta burst stimulation protocols will be carried out using a Magstim Super Rapid stimulator (Magstim Company, Whitland, UK) and a 70 mm figure-of-eight coil. TBS stimulation intensity will be set at 80% of the active motor threshold (AMT), defined as the lowest intensity which evoked at least five out of 10 MEPs with an amplitude > 200 μV peak-to-peak amplitude in the first dorsal interosseous (FDI) muscle during 10% of maximum voluntary contraction (56). This stimulation intensity was previously shown to produce plastic changes in the contralateral primary motor cortex (M1) (57). The iTBS protocol consists of a 2 s train of TBS repeated 20 times, every 10 s for a total of 190 s (48). The cTBS protocol consists of three-pulse bursts at 50 Hz repeated every 200 ms for 40 s (48). TBS will be applied over the lateral cerebellum, i.e., 1 cm inferior and 3 cm lateral to the inion (57). A cerebellar TBS is expected to modulate neural activity in the interconnected contralateral motor and parietal areas (57, 58). The coil will be positioned tangentially to the scalp, with the handle pointing superiorly; for sham TBS, it will be angled away so that no current was induced in the brain (59). Sham TBS will be delivered with an intermittent pattern in G1 and G2 and with continuous pattern in G3 and G4.

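### For G1 vs G2 and G3 vs G4 the group main effect subtracts session-2 from session-1 stimulation effects, and the plan does not name the term that tests active against sham

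*Protocol article*

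**What the plan says.** The Theta Burst Stimulation section allocates stimulation in a crossed order within each pair:

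- G1: "Group 1 (G1) will receive cerebellar iTBS before the session 1 and sham stimulation before the session 2"
- G2: "group 2 (G2) will receive cerebellar sham stimulation before the session 1 and cerebellar iTBS before the session 2"
- G3: "group 3 (G3) will receive cerebellar cTBS before the session 1 and sham stimulation before the session 2"
- G4: "group 4 (G4) will receive cerebellar sham stimulation before the session 1 and cerebellar cTBS before the session 2"

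Study Design gives two sessions, "each one including two behavioral tasks based on a modified SRTT paradigm". Behavioral Tasks places the second stimulation before delayed recall: "In DR, participants repeated the AD task after 45 min and following another stimulation protocol (according to group assignment". So MSL and AD follow the first stimulation, and DR and RA follow the second.

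Behavioral Task Analysis then names two factors, "groups: specifically, G1 vs. G2; G3 vs. G4; G1 vs. G3; G2 vs. G4; task; MSL, DA, DR, and RA", for both accuracy and response time. I read DA there as AD. No factor stands for the stimulation received, and no term or contrast is named as the test of the hypothesis. The Abstract expects "processing acceleration and reduction of error in all the conditions induced by cerebellar iTBS", with cTBS possibly doing the opposite.

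**The concern.** G1 vs G2 and G3 vs G4 are the only listed pairs that set one active stimulation against sham in every task. In each pair the group that is active in session 1 is sham in session 2, and the reverse. Averaging over the four tasks, as a group main effect does, subtracts the session-2 effect from the session-1 effect.

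Someone who opens the ANOVA table and reads the group line could report no effect of iTBS or cTBS when there is one. The omnibus interaction would pick up the signal, but with 3 degrees of freedom it does not say which tasks differ or in which direction. The plan names nothing that does.

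**Working it through.** **No figure to reproduce.** The article gives no power, effect size, SD or alpha.

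**Inputs from the article.** The order of stimulation by group, the assignment of tasks to sessions, the two ANOVA factors with the four pairs, and 40 participants in four groups.

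**Assumptions.** 10 per group (equal split), two-sided alpha 0.05, SD 1 in each task, and equal correlation rho between tasks. Let e be the effect of iTBS in a task; for the opposite effect cTBS is -e. Sham is 0.

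**Step 1: group differences in the order MSL, AD, DR, RA (equal effects, no carry-over).**

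| Pair | Cell differences | Main effect (mean of the four) |
|---|---|---|
| G1 - G2 | +e, +e, -e, -e | 0 |
| G3 - G4 | -e, -e, +e, +e | 0 |
| G1 - G3 | 2e, 2e, 0, 0 | e |
| G2 - G4 | 0, 0, 2e, 2e | e |

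If cTBS does nothing, the last two rows become e/2.

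**Step 2: relax the assumptions for G1 - G2.** Define the session contrast as half of [difference in the mean of MSL and AD, minus difference in the mean of DR and RA].

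| Case | Cell differences | Main effect | Session contrast |
|---|---|---|---|
| Equal effects, no carry-over | e, e, -e, -e | 0 | e |
| Session-2 effect half as large | e, e, -0.5e, -0.5e | 0.25e | 0.75e |
| Half of the session-1 effect carries over | e, e, -0.5e, -0.5e | 0.25e | 0.75e |
| Full carry-over | e, e, 0, 0 | 0.5e | 0.5e |

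The second and third cases give the same cell differences.

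**Step 3: power for G1 vs G2 with equal effects of d SD and no carry-over.** Each person's mean of MSL and AD minus mean of DR and RA has variance 1 - rho, and the groups differ by 2d on it. The noncentrality is therefore (2d)²/[2(1 - rho)/n] = 2n·d²/(1 - rho). The whole interaction lies in this one component, so the same value applies to the 3-df test on (3, 54) df and to the contrast on (1, 18) df. With n = 10 and d = 0.5 it is 5/(1 - rho).

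| rho | Noncentrality | Group main effect | 3-df interaction | 1-df session contrast |
|---|---|---|---|---|
| 0.3 | 7.14 | 0.05 | 0.57 | 0.71 |
| 0.5 | 10.0 | 0.05 | 0.73 | 0.85 |
| 0.6 | 12.5 | 0.05 | 0.83 | 0.92 |
| 0.7 | 16.7 | 0.05 | 0.93 | 0.97 |

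At d = 0.4 and rho = 0.6 the noncentrality is 8.0, and the three powers are 0.05, 0.62 and 0.76. Simulation (4,000 runs per setting) at d = 0.5 and rho = 0.3/0.5/0.7 gave 0.05 throughout for the main effect, 0.55/0.72/0.92 for the interaction and 0.71/0.85/0.97 for the contrast.

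**Step 4: would session 1 alone do?** The mean of MSL and AD has variance (1 + rho)/2 = 0.8 at rho = 0.6. The noncentrality for G1 vs G2 is 0.5²/(2 × 0.8/10) = 1.56, and power is about 0.22. A session-1 comparison is free of carry-over from an earlier stimulation, but it is too weak to be the main test and leaves out DR and RA.

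**The case against.** Four objections have force.

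- **Equal effects are not stated.** The Abstract and Discussion give a direction for iTBS, not an equal size in every task. One sequence runs through all four tasks and DR repeats AD, so carry-over is plausible. A reader might infer that the main effect is exactly zero under the trial's own hypothesis; the article does not support that. Step 2 shows that what is left is still only 0.25e to 0.5e in the cases tried, and it remains a difference between sessions.
- **Two of the four pairs do not cancel.** In G1 vs G3 and G2 vs G4 opposite effects add, and the main effect is e. This stands, but these pairs compare iTBS with cTBS, or sham with sham, and never active with sham.
- **The interaction keeps the signal.** A two-way ANOVA ordinarily includes group by task, and the article does not make the main effect the decisive test. A reader might infer that the analysis is blind to the hypothesis. It is not, as the interaction powers in Step 3 show. Coding by group also serves the stated aim of separating encoding from retrieval.
- **An article may leave contrasts to a fuller plan.** That is fair for detail. But this article does fix factors and pairs, and the listed group comparisons, read as main effects, give the wrong quantity for two pairs.

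A reader might also object that two-way repeated measures should read mixed ANOVA, since group is between participants. That is terminology: nothing suggests that group would be fitted as a within-participant factor.

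**Conclusion.** The point holds in a limited form. For G1 vs G2 and G3 vs G4 the group main effect contrasts session-1 with session-2 effects and does not estimate active versus sham. It is zero under equal effects without carry-over, and a fraction of the effect in the other cases examined. The information is in the planned model, in the session component of group by task, but the plan does not say so.

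Naming that component raises power at 0.5 SD by 0.04 to 0.14 over the omnibus interaction, for rho from 0.7 down to 0.3, and gives a signed estimate. The cancellation follows from the allocation alone. The power figures rest on the assumed group size, effect, equal correlation and absence of carry-over, none of which the article gives. Severity: should-fix.

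**What to change.** For G1 vs G2 and G3 vs G4:

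1. Pre-specify the 1-df Group x Session contrast, the mean of MSL and AD minus the mean of DR and RA compared between groups, as the test of active versus sham. Half of the group difference estimates the effect averaged over the two sessions when there is no carry-over. Staying within a pair also keeps the sham pattern the same on both sides (intermittent in G1/G2, continuous in G3/G4).
2. Follow it with the group contrast in each task. Those for MSL and AD are free of carry-over from an earlier stimulation.
3. State that the group main effect is not interpreted for these pairs, and that G1 vs G3 and G2 vs G4 address iTBS versus cTBS.

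The cost is analysis wording only, with the same data and model. The drawback is that the contrast shrinks if the session-1 stimulation carries over, to half with full carry-over. The MSL and AD contrasts help to show this, though with limited power (Step 4).

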## Materials and Methods

### Population

In this randomized, double blind experimental study, 40 healthy, right-handed participants were enrolled. Hemispheric dominance was assessed through the Edinburgh Handedness Inventory (EHI) (54). The inclusion criteria followed in the study were: (i) age 18–80 years, (ii) absence of visual or auditory disturbances possibly impacting on neuropsychological evaluation, (iii) no previous medical-neurological conditions considered as exclusion criteria for TMS (55), and (iv) no previous psychiatric diseases.

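### In G1 vs G2 and G3 vs G4 the group main effect compares stimulation orders, not stimulation; the test of TBS lies in group x task, which the analysis section does not name

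*Protocol article*

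**What the plan says.** The Protocol article, Behavioral Task Analysis, names two independent variables for both accuracy and response time: "groups: specifically, G1 vs. G2; G3 vs. G4; G1 vs. G3; G2 vs. G4; task; MSL, DA, DR, and RA". (DA there is evidently the adaptation task, called AD elsewhere.) The model is a two-way repeated measures ANOVA. The section names no stimulation or session term, no interaction and no contrast.

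The Theta Burst Stimulation section fixes what each group receives: "Group 1 (G1) will receive cerebellar iTBS before the session 1 and sham stimulation before the session 2", and "group 2 (G2) will receive cerebellar sham stimulation before the session 1 and cerebellar iTBS before the session 2". G3 and G4 follow the same scheme with cTBS. Study Design describes "two experimental sessions on a single-day, separated by a break of 45 min, each one including two behavioral tasks"; by the Behavioral Tasks section these are MSL and AD in session 1, then DR and RA in session 2. That section adds: "In DR, participants repeated the AD task after 45 min and following another stimulation protocol".

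The Abstract predicts "processing acceleration and reduction of error in all the conditions induced by cerebellar iTBS", and the Discussion repeats this for all phases, with the opposite expected of cTBS.

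**The concern.** G1 vs G2 and G3 vs G4 are the two planned comparisons that set an active stimulation against its own sham. Within each pair both groups receive both treatments, so the group factor says only which came first. Averaged over the four tasks, each group has been active half the time, and an effect in the predicted direction in every condition enters the group difference twice with a plus and twice with a minus.

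Two misreadings are then possible. A null group effect could be reported as no effect of TBS when it carries almost no information on that question. A significant group x task test could be reported as an effect of TBS when the omnibus F shows only that the two profiles differ somewhere; it gives no direction and could arise from differences tied to the hand used.

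**Working it through.** The article gives no sample-size calculation, effect size, SD or alpha, so there is no figure of its own to reproduce.

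**Inputs from the article.** 40 participants (Population), four groups (Study Design), and the stimulation order by group (Theta Burst Stimulation).

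**Assumptions.** Equal groups, so 40 / 4 = n = 10 each; SD 1 in each task; equal within-person correlation rho between tasks; two-sided alpha 0.05; an active-minus-sham effect d that is the same in all four tasks; a fraction c of the session-1 effect retained into session 2.

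**Step 1: expected G1 minus G2 difference by task.**

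| Task | G1 | G2 | Difference |
|---|---|---|---|
| MSL | active | sham | +d |
| AD | active | sham | +d |
| DR | sham | active | cd - d |
| RA | sham | active | cd - d |

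G3 minus G4 has the same pattern with the cTBS effect.

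**Step 2: group main effect** (mean of the four differences).
- c = 0: (d + d - d - d)/4 = 0
- c = 0.5: (d + d - 0.5d - 0.5d)/4 = 0.25d
- c = 1: (d + d + 0 + 0)/4 = 0.50d
- c = 0, MSL effect doubled: (2d + d - d - d)/4 = 0.25d

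With c = 0 it is zero whenever the MSL and AD effects sum to the same as the DR and RA effects.

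**Step 3: group x session contrast**, mean(MSL, AD) - mean(DR, RA), compared between groups. Its expectation is d - (cd - d) = (2 - c)d: the session-1 effect plus the session-2 effect minus what is retained. That is 2d, 1.5d and d for c = 0, 0.5 and 1.

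**Step 4: power at d = 0.3, rho = 0.7, c = 0.**
- Group main effect: difference 0, so 5% (alpha only).
- Group x session, 1 df: per-person variance 1 - rho = 0.3; standard error sqrt(2 x 0.3/10) = 0.245; noncentrality 0.6/0.245 = 2.45 on 18 df; power 64%.
- Group x task, 3 df: noncentrality (n/2) x 4d²/(1 - rho) = 5 x 0.36/0.3 = 6.0 on F(3, 54); power 49%. This is 2.45 squared: the same signal spread over 3 df.
- Group x (AD vs DR), 1 df: per-person variance 2(1 - rho) = 0.6; standard error sqrt(2 x 0.6/10) = 0.346; noncentrality 0.6/0.346 = 1.73; power 37%.

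**Step 5: range over the assumptions.**

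| d | rho | c | Group effect | Group x task, 3 df | Group x session, 1 df | AD vs DR, 1 df |
|---|---|---|---|---|---|---|
| 0.3 | 0.5 | 0 | 5% | 30% | 44% | 25% |
| 0.3 | 0.7 | 0 | 5% | 49% | 64% | 37% |
| 0.3 | 0.7 | 0.5 | 5.4% | 29% | 41% | 23% |
| 0.5 | 0.5 | 0 | 5% | 73% | 85% | 56% |
| 0.5 | 0.5 | 0.5 | 6% | 46% | 61% | 35% |
| 0.5 | 0.5 | 1 | 10% | 22% | 32% | 19% |
| 0.5 | 0.7 | 0 | 5% | 93% | 97% | 78% |

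**Step 6: the other two pairs.** For G1 vs G3 and G2 vs G4, with iTBS at +d and cTBS at -d and no carry-over, the groups differ by 2d in the active session and 0 in the other. The main effect is (2d + 2d + 0 + 0)/4 = d: halved, not cancelled.

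**The case against.** The strongest defence is that the signal is already in the model. Stimulation is fully determined by group and task, a two-way ANOVA ordinarily includes their interaction, and the article nowhere says that the group main effect is the test of interest. At d = 0.5 and rho = 0.7 the omnibus interaction has 93% power. A condensed article may also leave follow-up contrasts to a fuller plan. This stands: the model need not change, and the gap lies in which term is named and how it is read.

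Three stronger readings are tempting, and the article does not support them.

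- A reader might infer that the group effect is exactly zero under the trial's own hypothesis. The article predicts direction in all conditions, not equal size or absence of carry-over. Cancelled or heavily diluted is as far as it goes.
- A reader might infer that the active-sham swap between AD and DR is never tested. It is one component of the 3-df interaction, so it is tested but not isolated.
- A reader might take AD vs DR as the only clean comparison. It is the one task repeated as such under swapped stimulation, but DR can retain session-1 effects. G1 vs G2, or G3 vs G4, at MSL and at AD is also active against sham on one task, and is free of carry-over between sessions, though weak (about 18% power at d = 0.5). Like for like, AD vs DR alone is also weaker than the omnibus test: 78% against 93% at d = 0.5, rho = 0.7.

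A last objection is that the Discussion hopes to separate encoding from retrieval, which a pooled contrast cannot do. That is correct, and is why the condition-specific differences are needed beside it.

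**Conclusion.** The point holds for G1 vs G2 and G3 vs G4 only. There the group main effect is not a test of stimulation. It keeps at most half of a common effect even with full carry-over, and its power stayed between 5% and about 10% in the settings tabulated. This part follows from the stimulation schedule and needs only that TBS acts in the same direction in all conditions with similar size.

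The gain from naming a 1-df contrast is more modest and depends on the assumptions. Over the 3-df interaction it is 15 percentage points at d = 0.3 and 4 at d = 0.5 (rho = 0.7, no carry-over), if effects are similar across conditions. The firmer gain is a signed estimate in place of a directionless F. The group sizes, effect sizes, correlations and alpha are assumptions, since the article states none of them.

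**What to change.** In Behavioral Task Analysis:

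1. State that for G1 vs G2 and G3 vs G4 the stimulation test is the 1-df group x session contrast (MSL and AD against DR and RA) within group x task, and that the group main effect is not interpreted as a stimulation effect. Add that the contrast is the session-1 effect plus the session-2 effect, less any retained session-1 effect.
2. Report the four condition-specific differences, each signed as active minus sham, with 95% confidence intervals. Note that MSL and AD are free of session carry-over, while DR and RA may include retained session-1 effects.
3. Give group x (AD vs DR) as a secondary same-task contrast, noting that under equal effects it has less power than the omnibus test and that any retained session-1 effect reduces it.

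The cost is analysis wording: no new data, participants or procedures. The small downside is that the pooled contrast averages over conditions and does not separate encoding from retrieval, which must be read from the intervals in item 2.
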